## Abstract

Type 1 Wolfram syndrome is a rare, neurodegenerative pathology characterized by the association of insulin-dependent diabetes and optic atrophy. Other symptoms include diabetes insipidus, hearing loss and neurological damage. Fecal incontinence was recently recognized as a new symptom. Its pathophysiological mechanism remains unknown. We plan to collect data on the severity of the syndrome at the onset of fecal incontinence, the frequency of signs suggestive of pons volume reduction, and the frequency of urinary disturbances. Based on this information, we will investigate the possible location of the neurological involvement causing this symptom.

## Introduction

Wolfram syndrome (WS) is a rare, autosomal recessive neurodegenerative pathology, the prevalence of which is estimated at 1/830,000 people (1/55,000–1/700,000 according to Barrett) (Barrett and Bundey, 1997). WFS1 is the main gene involved, responsible for type 1 WS (WS1) (MIM #222300), while the CISD2 gene is responsible for type 2 WS (MIM #604928) (Amr et al., 2007, Inoue et al., 1998). WS1 is characterized by the association of insulin-dependent diabetes and optic atrophy, both occurring before the age of 16 according to EuroWABB guidelines (EuroWAAB, 2014). Other symptoms may occur, such as diabetes insipidus, sensorineural hearing loss, neurological damage, and urinary tract abnormalities (Karzon et al., 2018, Washington University Wolfram Study Group, 2013, Urano, 2016). These vesico-sphincter disorders during WS1 are linked to multiple factors: neurological disorders responsible for a neurological bladder, diabetes insipidus, insulin-dependent diabetes (Ribière et al., 2013, Rove et al., 2018). These well-known disorders are subjects of numerous studies that describe them or discuss their management.

Surprisingly, the French patient association reported to our rare disease center dedicated to Wolfram syndrome that some patients presented with ano-sphincteric dysfunction, which they had never dared to discuss. These symptoms were never mentioned because the patients and their family were not specifically sought during consultations and were very embarrassed. This condition must be considered as debilitating for the patients, who are deeply ashamed of it. Furthermore, these patients believed that these symptoms should not be linked to their condition since they are not part of the "classic list" of symptoms and were never brought up at family meetings. A preliminary study was conducted based on a questionnaire sent to patients with Wolfram syndrome followed in our rare disease center or to patients, who attended to therapeutic education sessions. In this study, 45.95%. of the WS1 patients complained with such severe and disabling problem ([name], 2025). The importance of this frequency allowed us to conclude that these ano-sphincteric disorders are a real and new symptom of WS. It must be taken into account by physicians and treated as such.

To date, there is no clear data to determine the mechanism(s) involved in explaining the occurrence of this sphincter disorder during WS. However, it is essential to differentiate the mechanism and the location of the damage leading to these different causes of ano-sphincteric disorders. In the absence of studies on this subject, we are reduced to making hypotheses concerning these physio pathogenic mechanisms.

## Scientific rationale

In a preliminary study that we conducted, a questionnaire was sent to 37 patients with Wolfram syndrome followed by our department or who had only participated in therapeutic education sessions ([name], 2025). These patients come from all over the country. We received 25 answers. Among those 25 answers, 17 patients reported fecal incontinence and constipation (68.00%). However, to avoid bias, we considered that people who did not respond did not have a fecal incontinence disorder. Thus, the percentage of patients suffering from fecal incontinence and constipation was 45.95% ([name], 2025). The severity of this disorder, evaluated by patients, is high, rated at 8.23 + /- 2.86 on an analogic scale (range 2–10). This allows us to confirm that these ano-sphincteric disorders are a real symptom of WS and must be taken into account and treated as such even though this symptom needs to be confirmed by other teams. The management of these ano-sphincteric disorders is difficult. It requires methods ranging from the simplest dietary advice to more complex techniques for restoring transit control in the literature (Coggrave et al., 2014, Emmanuel, 2010). Understanding this mechanism of this fecal incontinence is not trivial and will have an impact on the therapies that may or may not be offered. This is a reason for justifying the present study.

It is important to determine whether the impairment of anal sphincter control is located in the terminal portion of this pathway or higher up in the brainstem. Knowledge of this location is mandatory to help further specific treatment development.

Neuroradiological studies have clearly demonstrated that brain-stem atrophy is highly possible since patients present with such degenerative involvement (Lugar et al., 2019). According to clinical data, reduction of pons volume, is responsible for swallowing disorders and sleep apnea (Licis et al., 2019). That is why we would look for these symptoms. The hypothesis is that a greater frequency of symptoms should indicate that ano-sphincteric disorders are the consequence of a reduction of pons volume. There will be no difficulty detecting swallowing disorders and sleep apnea. These symptoms are frequently encountered and patients report them spontaneously. They are usually worried about swallowing disorders. In addition, sleep apnea is responsible for chronic fatigue reported by patients, as well as non-restorative sleep. Therefore, the risk of overlooking either of these disorders and any potential association will be limited.

We will not focus on other symptoms such as endocrine disorders with delayed puberty. These symptoms require precise measurements, which are often not performed. Furthermore, these abnormalities tend to point more towards pituitary involvement. Yet, it is not certain that such involvement would be accompanied by damage to the neurological pathways. We will only look for the existence of diabetes insipidus due to associated hydro-electrolytic imbalances. Such imbalances have a potential role in altering stool consistency and may be associated with changes in bowel movements.

The second hypothesis that we will test is that the neurological damage leading to ano-sphincteric disorders could be located in the lower part of the spinal cord (Preziosi et al., 2013). According to literature, such location will lead to an impairment of voluntary control of the anal sphincter due to a reduction of the perception of anorectal fullness which facilitates sphincter control and anticipation of defecation needs (Magnuson et al., 2023, Preziosi et al., 2013). This hypothesis is supported by a similarity of complaint between ano-sphincteric disorders and urinary disorders as reported by patients. The urgency to defecate, leading to ejection of anal content despite efforts to prevent such disastrous situation, is similar to urination due to engorgement and lack of proper bladder emptying. It constitutes a good relationship to test the hypothesis of a localization of the damage at this level. We expect that if this hypothesis will be confirmed, we will find statistically significant association urinary and anosphincteric disorders without any manifestation of pons atrophy. A limitation of this study will be association of swallowing disorders or sleep apnea and lower urinary tract dysfunction. In such case, we will not be able to distinguish between lesions located high in the brainstem and those affecting the spinal cord. Urinary problems can also be due to reduction of pons volume (Rove et al., 2018).

Finally, there is another hypothesis based on the existence of few specific mutations in the WFS1 gene leading to a particular SW1 phenotype with anosphincteric disorders. Lee et al. have clearly shown that the type of mutation can modify the severity of symptoms linked to the WFS1 gene (Lee et al., 2023).

In case of the absence of clear statistically significant association allowing to evoke a degenerative neurological mechanism, we will consider a last hypothesis. There is a rational based on the literature to consider that anosphincteric disorders could be related to dysautonomic disorders observed in childhood type 1 diabetes (Roche et al., 2005, Tang et al., 2013).

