## Method

The method we intend to implement will be based on data from literature concerning the possible neurological origin of fecal incontinence. A neurological mechanism will be considered given the pathophysiology of WS, which is a neurodegenerative condition (Barrett et al., 1993, Barrett and Bundey, 1997, Urano, 2016). It is well known that neurological or ENT symptoms, such as swallowing disorders, will appear during the course of WS (Marshall et al., 2013). However, in order not to overlook variations related to patient mutations, we will add to this study a genetic component. Marshal and other authors demonstrated that the severity of the symptoms during WS is related to the type of mutations harbored by the patients (Marshall et al., 2013)^.^.

In order to determine the mechanism of ano-sphincteric disorders, we will divide the patients into two subgroups according to the presence or absence of ano-sphincteric disorders.

According to this generic mechanism, we will collect different parameters that will be used in the analyses: the duration of the WS, the duration of insulin type I diabetes, the values of glycosylated hemoglobins over this period, the age of patients as well as their visual acuity at first occurrence of ano-sphincteric disorders and the presence of vesico-sphincter disorders, swallowing disorders or sleep apnea (Hoekel et al., 2014).

Firstly, we intend to characterize the severity of the WS in each patient as the occurrence of ano-sphincteric disorders. To that end, we have planned to consider more specifically three parameters from patient’s files for a multi-factorial analysis. We will consider the age of our patients when ano-sphincteric disorders were mentioned for the first time as well as the duration of WS and the duration of insulin type I diabetes at the time of the first mention of this symptom. This duration will be calculated from the age of the first symptom of WS, whatever it may be. These data will be based solely on patient self-reporting. We have no way to increase the reliability of this data. However, this limitation will be taken into account in the analysis. We will collect the LogMAR far best corrected visual acuity at four or one meters according to the number of letters read.

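### The plan turns an association with swallowing disorders and sleep apnea into a causal conclusion about pons volume, which none of its listed variables measures

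*Protocol article*

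**What the plan says.** All references are to the protocol article.

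- **Scientific rationale, first hypothesis.** Clinical data are cited to the effect that "reduction of pons volume, is responsible for swallowing disorders and sleep apnea". The inference to be drawn follows: "The hypothesis is that a greater frequency of symptoms should indicate that ano-sphincteric disorders are the consequence of a reduction of pons volume".
- **Ascertainment, same section.** "There will be no difficulty detecting swallowing disorders and sleep apnea", and "These symptoms are frequently encountered and patients report them spontaneously".
- **Abstract.** What will be collected is described more cautiously, as "the frequency of signs suggestive of pons volume reduction".
- **Method and Statistics, variables.** The lists contain the durations of WS and diabetes, glycosylated hemoglobin, age, visual acuity, WFS1 mutation type, diabetes insipidus and "the presence of vesico-sphincter disorders, swallowing disorders or sleep apnea". No imaging or pons volume is listed.
- **Method, disease course.** "It is well known that neurological or ENT symptoms, such as swallowing disorders, will appear during the course of WS".
- **Scientific rationale, second hypothesis.** The spinal-cord reading needs a statistically significant link between urinary and ano-sphincteric disorders with no sign of pons atrophy. The limitation conceded there is that brainstem and cord cannot be told apart when swallowing disorders or apnea coexist with lower urinary tract dysfunction.
- **Statistics.** Symptom associations are tested by chi-square, with an exploratory univariate analysis of four symptoms and a threshold of 0.05.

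**The concern.** The premise is that pons reduction causes the symptoms. The inference runs the other way, from symptoms to pons reduction, and then on to pons reduction as the cause of a third condition. This needs the two symptoms to be reasonably specific to the pons, and it needs no other factor to link them to ano-sphincteric disorders. The article argues for neither. Its own remark that swallowing disorders appear as WS progresses supplies a competing explanation: patients with more advanced disease may have both.

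The opposite error is also open. Both symptoms are taken from files and rest on what patients report. If the proxy misses or misattributes cases, a true pons association is diluted. Where a significant urinary association is also present, the second hypothesis would then favour the cord.

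The article says that knowing the location is needed to develop specific treatments, so an unsupported localisation has consequences.

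**Working it through.** **1. Is there a figure to reproduce?** No. The article states no sample size, power, symptom frequency or proxy accuracy for this study. The point rests on the text, and the calculations below only show direction and plausible size.

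**2. The text side by side.**

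| Step in the argument | What the article provides |
|---|---|
| Pons reduction leads to swallowing disorders and apnea | Stated, with a citation |
| Swallowing disorders and apnea imply pons reduction | Not argued; no sensitivity or specificity |
| Pons reduction is the cause of ano-sphincteric disorders | Read from symptom frequency |
| Pons observed directly | No such variable listed |
| Other routes to the symptoms | Swallowing disorders said to appear with the disease course |

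**3. An association without a pons difference (assumed inputs).** Pons reduction is 40% in both groups. Proxy sensitivity is 0.7. A non-pons cause is present in a proportion *q* of affected patients and in 10% of unaffected patients.

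Symptom frequency = 1 − (1 − 0.40 × 0.7)(1 − *q*) = 1 − 0.72(1 − *q*).

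Unaffected: 1 − 0.72 × 0.90 = 0.352.

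Group sizes come from the preliminary questionnaire, for illustration only. It was sent to 37 patients, 25 answered and 17 reported the disorder. Counting non-respondents as unaffected gives 17 versus 20; respondents alone give 17 versus 8. The rejection rate is that of the uncorrected two-sided chi-square at 0.05, by exact enumeration of the binomial tables.

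| *q* in affected | Frequency, affected | Odds ratio | 17 v 20 | 17 v 8 |
|---|---|---|---|---|
| 10% (no difference) | 0.352 | 1.00 | 5.0% | 4.7% |
| 20% | 0.424 | 1.36 | 7.7% | 5.3% |
| 30% | 0.496 | 1.81 | 15.0% | 9.0% |
| 40% | 0.568 | 2.42 | 26.7% | 15.9% |

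Pons involvement is identical in the two groups in every row.

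**4. Dilution of a true pons association (assumed inputs).** Pons reduction is 60% in affected and 27% in unaffected patients. True odds ratio = (0.60/0.40)/(0.27/0.73) = 4.06.

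Observed frequency = *p* × Se + (1 − *p*)(1 − Sp).

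| Se | Sp | Affected | Unaffected | Observed odds ratio |
|---|---|---|---|---|
| 0.5 | 0.6 | 0.460 | 0.427 | 1.14 |
| 0.7 | 0.75 | 0.520 | 0.372 | 1.83 |
| 0.9 | 0.9 | 0.580 | 0.316 | 2.99 |

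Over Se 0.5-0.9 and Sp 0.6-0.9 the observed odds ratio runs from 1.1 to 3.0.

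**The case against.** The strongest defence is that this is a hypothesis tested through a clinical proxy. The key sentence is introduced as a hypothesis, the Abstract speaks of suggestive signs and a possible location, and the Statistics section calls the four-symptom analysis exploratory and looks for association. That is fair and limits the seriousness. It does not remove the point: the sentence says what a higher symptom frequency should indicate, and that is a cause in a named structure. The Method section repeats the aim of specifying the location.

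The conceded limitation is also real, but it covers only coexisting urinary dysfunction. It does not cover non-pons causes or unreported symptoms. The multi-factorial analysis relates WS severity to swallowing disorders and apnea; no adjusted test of ano-sphincteric disorders on these symptoms is stated. Adjustment would in any case not make the symptoms pons-specific.

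Four stronger readings are tempting, and the documents do not support them:

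- *A null pons result alone yields a cord verdict.* It does not. A significant urinary association is also required, and with no clear association the article turns to dysautonomia.
- *The symptoms are shown to be non-specific.* They are not. The remark on disease course names no particular non-pons cause, and the cited sources are not at hand. The article merely gives no ground for assuming specificity.
- *The false-association rate of this study is 27%.* That is one assumed point. It needs a non-pons cause four times as common in affected patients. The split of 17 versus 20 also counts non-respondents as unaffected, whereas this study keeps only files that clearly record presence or absence.
- *The plan is defective for not requiring MRI.* Nothing says that the files hold brain scans. Using clinical signs in a retrospective file review is a legitimate choice, and a small, selected imaging subset would be a poor gatekeeper for the conclusion.

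**Conclusion.** The concern holds as a limit on what may be concluded. The listed data can show whether swallowing disorders and sleep apnea are more frequent in patients with ano-sphincteric disorders. By themselves they cannot show that those disorders result from reduced pons volume, and the lack of such an association cannot by itself show that the pons is spared.

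The size cannot be fixed from the documents. Under the stated assumptions, an association arises without any pons difference in about 8-27% of studies (17 v 20) or 5-16% (17 v 8), and a true odds ratio of about 4 appears as 1.1-3.0. At the mild end the first effect is scarcely above the nominal 5%. The conclusion rests on the direction of the inference in the text and does not depend on these figures. The study remains feasible; only its anatomical claim goes beyond its data.

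**What to change.** 1. In the Scientific rationale, replace the inference sentence with wording such as: *A greater frequency of swallowing disorders or sleep apnea will be reported as an association with brainstem-type clinical signs. It will not by itself be taken as evidence that reduced pons volume causes the ano-sphincteric disorders.*
2. In the same section, word the cord reading as a significant urinary association *without associated swallowing disorders or sleep apnea*, in place of the absence of pons atrophy.
3. Optional: if brain MRI reports happen to be in the files, describe pons or brain-stem atrophy by group and against the two symptoms. Treat this as supportive information only, not as a condition for the conclusion.

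The first two changes are wording only and need no new data. The third adds one extraction item, possibly available for few or no patients. The price is a more modest headline: an association with clinical signs, not a demonstrated anatomical cause.

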## Patients and methods

### Patients

We will conduct a retrospective study based on the analysis of files of patients followed in the Reference Center for Rare Diseases in Ophthalmology since 2018. We will only retain files in which the presence or absence of sphincter disorders is clearly mentioned. Although this symptom is systematically sought during consultations and day hospitalization by the referring physician of the Centre, there is a risk that some patients may not have declared it.

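### Swallowing disorder and sleep apnea rest on spontaneous report, with no stated rule for an unrecorded sign, although their absence counts as evidence for a spinal site

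*Protocol article*

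**What the plan says.** **Pons signs.** Swallowing disorder and sleep apnea are the article's clinical markers of reduced pons volume. The Scientific rationale says of them: "There will be no difficulty detecting swallowing disorders and sleep apnea. These symptoms are frequently encountered and patients report them spontaneously". It concludes that few will be overlooked. It describes no prompted question, no test and no rule for a file that is silent on either sign.

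**How the signs are used.** The same section would regard the spinal hypothesis as confirmed by a significant association between urinary and ano-sphincteric disorders when pons signs are missing. If no clear association appears, it turns to a dysautonomic explanation linked to diabetes.

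**Group status.** Under Patients, a file is kept only if it explicitly records whether a sphincter disorder is present or absent. The section adds that "this symptom is systematically sought during consultations and day hospitalization by the referring physician of the Centre", and admits that some patients may still not have declared it. The Introduction, however, says of the same symptom: "These symptoms were never mentioned because the patients and their family were not specifically sought during consultations and were very embarrassed".

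**Preliminary survey.** According to the Scientific rationale, "a questionnaire was sent to 37 patients with Wolfram syndrome" and "We received 25 answers"; 17 of the replies were positive. The 12 non-responders were counted as unaffected: "to avoid bias, we considered that people who did not respond did not have a fecal incontinence disorder". The resulting 45.95% is repeated in the Introduction without that rule.

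**The concern.** In this study the absence of a pons sign is a finding in its own right, because it separates the spinal reading from the brainstem reading. A retrospective file that says nothing about swallowing or sleep is not the same as one recording that the patient was asked and had no complaint. The article protects the grouping variable against this confusion but gives the pons signs no comparable protection. Missed signs would cost power, and they could also move the conclusion about the site of the lesion toward the spinal cord or the fallback explanation.

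Two smaller matters belong here. The two statements on whether bowel symptoms were asked about need a date to be compatible. The survey figure is described as guarding against bias when it is the lowest value the data allow.

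**Working it through.** **1. The article's own figures.** Inputs from the Scientific rationale: 37 questionnaires, 25 replies, 17 positive.
- Responders only: 17/25 = 68.00%, as printed.
- Non-responders counted negative: 17/37 = 45.95%, as printed.
- Non-responders: 37 − 25 = 12. All counted positive: (17 + 12)/37 = 78.4%.
- Width of the range: 12/37 = 32.4 percentage points. If the 17 positive replies are true, 45.95% is the minimum.

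**2. Ascertainment, side by side.**

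| Item | How it reaches the file | Rule for a silent file |
|---|---|---|
| Ano-sphincteric disorder (defines the groups) | Asked by the referring physician (Patients) | File not retained |
| Swallowing disorder, sleep apnea | Volunteered by the patient (Scientific rationale) | None stated |
| Urinary disorder | Listed among the data to collect (Method) | None stated, unless the unqualified term in Patients also covers the bladder |

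If the retention rule does cover the bladder, urinary signs are better protected than pons signs, which widens the imbalance.

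**3. Size of the effect if silence is read as absence (illustration).** Assumptions, none from the article: a pons sign truly present in 60% of patients with the bowel disorder and 30% of those without; a fraction r of true signs recorded, equal in both groups; no false positives; group status correct; 37 files split 17 and 20 as in the survey; two-sided 5% test.

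Observed frequencies: e1 = 0.60r and e0 = 0.30r. Odds ratio = [e1/(1 − e1)]/[e0/(1 − e0)]. Share of affected patients who appear free of the sign = 1 − e1. Power = Φ{[e1 − e0 − 1.96√(p(1 − p)(1/17 + 1/20))]/√(e1(1 − e1)/17 + e0(1 − e0)/20)}, with p the pooled frequency.

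| r | e1 | e0 | Odds ratio | Affected, no sign on file | Power |
|---|---|---|---|---|---|
| 1.0 | 0.60 | 0.30 | 3.50 | 40% | 44.7% |
| 0.8 | 0.48 | 0.24 | 2.92 | 52% | 32.9% |
| 0.6 | 0.36 | 0.18 | 2.56 | 64% | 23.5% |

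For example, at r = 0.8 the odds ratio is (0.48/0.52)/(0.24/0.76) = 2.92. Under-recording weakens the pons association and enlarges the group that looks free of pons signs.

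**4. Undated absent entries (secondary illustration).** Let P be the true prevalence and s the assumed share of true cases who declare the symptom. True cases among those recorded absent = P(1 − s)/(1 − Ps).
- P = 45.95%: 7.8%, 14.5% and 20.3% for s = 0.9, 0.8 and 0.7.
- P = 68%: 17.5%, 29.8% and 38.9%.

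The values of s are assumed. The article gives no date from which to tell how many absent entries came before systematic asking.

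**The case against.** The strongest reply is that the article never says a silent file counts as negative for swallowing or apnea. It gives a reason to expect these signs in the files: patients worry about swallowing and report fatigue and unrefreshing sleep. Coding of unrecorded items may sit in the full protocol. This stands in part: negative coding is an inference and is treated here as a condition. The article nevertheless asserts that detection will be easy and few signs overlooked, and it attaches a conclusion to their absence.

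A reader might infer that controls, too, are patients whose files are merely silent. The documents do not support that. Patients excludes such files, describes prompted asking and concedes under-declaration. What remains is false or undated negative answers.

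A reader might also carry the Introduction's account of concealment over to the pons signs. That account concerns an embarrassing bowel symptom that patients thought unrelated to their disease. It reaches swallowing and apnea only by analogy and is not used as evidence here.

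The tilt toward the spinal pattern also requires the urinary association to survive. If urinary signs are under-recorded as badly as pons signs, both associations weaken, and the outcome is more likely to be inconclusive. This is correct, and is one reason to code urinary disorder in the same way.

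Finally, 45.95% feeds no sample size or test, its derivation is disclosed, and a low figure is cautious for the claim that the symptom is real. All true; only the label and the missing range are at fault.

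**Conclusion.** The point holds in conditional form. Detection of the pons signs rests on spontaneous report, no rule is stated for an unrecorded sign, and their absence is used to locate the lesion. If unrecorded is read as absent, the odds ratio in the illustration falls from 3.50 to 2.92 or 2.56, and affected patients who appear free of the sign rise from 40% to 52% or 64%. These sizes depend on the assumed 60% and 30% frequencies and on equal under-recording in both groups. If recording differs between groups, the bias could run either way.

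Secondary: the Introduction and Patients disagree on whether ano-sphincteric symptoms were asked about in consultations. They can be reconciled if asking began at some point, but the article does not give that date. It does not follow that absent entries in the files are generally unreliable.

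Minor: 45.95% is a lower bound described as a protection against bias. The planned analyses do not depend on it.

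**What to change.** **Main change.** At file review, code swallowing disorder, sleep apnea and urinary disorder each as *present*, *recorded absent* or *not recorded*. Report the associations twice: with *not recorded* excluded, and with it set to absent. Draw the spinal conclusion only if it holds in both analyses and the pons signs are recorded as absent, not merely unrecorded. Show the number not recorded per sign in each group. Withdraw the statement that detection poses no difficulty, or support it.

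**Cost.** One extra code per symptom. The analysis that excludes *not recorded* has fewer files and wider intervals, which matters in a small series. It may also select patients if positive findings are charted more readily than negative ones. Setting *not recorded* to absent errs through missed signs, so neither analysis should stand alone.

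**Secondary.** State when systematic asking about ano-sphincteric symptoms began, reconcile the Introduction with Patients, and repeat the group comparison without patients whose only absent entry predates it. The cost is one date per such file.

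**Wording.** In the Introduction and the Scientific rationale, call 45.95% (17/37, all 12 non-responders counted negative) a lower bound, give 68.0% among responders and 78.4% as the upper bound, and remove the claim that the rule avoids bias. This costs nothing.
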